## Data collection and management

### Plans for assessment and collection of outcomes {18a}

#### Description of clusters prior to baseline data collection

Prior to enrolment and baseline data collection, a total of 56 clusters will be identified using pre-trial census data, to ensure there are enough households with children ≤ 5 years of age to meet the sample population. Additional household enumeration activities will be conducted to validate this information, and clusters will be reselected where necessary. Clusters will be defined as discrete villages and mapped using mapping software (ArcGIS/QGIS) [20, 21]. Households will be enrolled to the trial by obtaining consent from the head of household, which will enable the household to receive the Mossie-GO™ device. Once enrolled into the trial, households will receive a unique identification number which will be used for all future data collection activities.

#### Malaria prevalence monitoring

One hundred children per cluster at baseline and sixty children per cluster at months 6 and 12, selected at random from separate households, will be sampled for malaria infection. A master list of households will be generated listing households with children ≤ 5 years of age and households will be randomly selected with replacement at each of the time points. If there are multiple children ≤ 5 years of age within the household, the Kish Grid method will be used to select the participant [22]. The study will be explained and consent obtained from the child’s parent/guardian before enrolling the child in the study. Once enrolled, the age and sex of the participant, along with use of other vector control products and antimalarial drugs will be recorded. A fingerstick blood sample will be taken for malaria RDT, a blood smear for analysis by microscopy and a blood spot for analysis by PCR at a later date. All participants will be eligible for malaria treatment, if they test positive by RDT at any sampling time point. This will be accessed following national standard of care guidance at their local health care facility or through the VHTs. Trained laboratory technicians will be responsible for blood sampling, reading and recording results and sample analysis via microscopy and PCR. Microscopic examination of slides will be conducted two times, independently in verified reference laboratories. Participant data and results will be collected manually on paper logs and then entered into Open Data Kit (ODK) software [23].

#### Household survey

A questionnaire will be presented to the head of household at the point of malaria sampling to assess household characteristics and behaviours which may impact study outcomes. Questions within the survey will include, but not be limited to housing classification (urban, peri-urban, rural), housing characteristics (size, ventilation, construction materials), family structure (multiple families inhabiting one household, one family inhabiting multiple household structures etc.), number of children ≤ 5 years of age sleeping in the room with the Mossie-™unit, inhabitant(s) occupation(s), use of alternative vector control tools, whether occupants slept under a bed net the night before the survey, socio-economic status, number of inhabitants and their age and presence of domesticated animals (density and location). This survey will be conducted by the data collectors responsible for obtaining informed consent. All data will be inputted directly to forms on ODK.

#### Acceptability of Mossie-GO™

##### Surveys/interviews

A questionnaire will be presented to the head of household at the point of malaria sampling at months 6 and 12 to assess the household’s experience and opinions of the Mossie-GO™ device. This will explore whether households have had positive or negative experiences with Mossie-GO™, whether household members would recommend Mossie-GO™ to other people and willingness to pay. This survey will be conducted by the data collectors responsible for obtaining informed. All data will be entered directly to forms on ODK.

##### Focus group discussions

FGDs will also be conducted to explore acceptability of the intervention, including factors such a willingness to pay and product design. Approximately 8–12 FGDs will take place, containing 6–10 participants. Groups will include a range of participants, for example, local community members, VHTs and district health officials. The discussions will be audio-recorded and transcribed.

##### Entomological monitoring

Within each of the 56 clusters, CDC light trap collections will be conducted in 7 households from 7 pm–7 am at baseline, 6 and 12 months to allow assessment of the impact of intervention on the density of *Anopheles* mosquitoes indoors. Data collectors will be trained in setting up and taking down CDC light traps and heads of households may be trained to switch on/off the traps at the required time when necessary. Households will be selected at random for CDC light trapping at each timepoint. Additionally, HLCs will be performed indoors and outdoors for 3 consecutive nights in 3 households within each of 10 clusters (30 households total) at baseline, 6 and 12 months to determine the effect of the intervention on the host seeking behaviour of mosquitoes. Alongside the data collector, the head of household and community members will be trained to conduct the HLC and will be supervised during data collection. The clusters and households selected for HLCs will be selected at random for each time point.

Caught mosquitoes from CDC light trapping and HLCs will be examined to record vector species diversity, density and sporozoite rates at each time point. To characterize the insecticide resistance profile of the vector population in the study area, a series of WHO tube tests will be conducted in both districts (Jinja and Buikwe). Larval dipping will be conducted at selected sites, with larvae reared to adults in laboratory facilities and tested for insecticide resistance following WHO protocols and using standard WHO data collection forms [24].

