### Trial design {8}

This trial is a double-blinded placebo controlled cRCT with two arms. A total of 56 clusters will be randomly assigned, in a 1:1 ratio, to one of the two arms to receive the intervention or the placebo control. The intervention is a Mossie-GO™ device, containing a transfluthrin-treated disc which sits above a fan powered by solar energy (Fig. 1). The control arm will receive the Mossie-GO™ device with an identical looking disc with no active ingredient. All eligible, consenting households will receive a single Mossie-GO™ device with 5 W solar panel, and discs will be replaced at monthly intervals. The device requires 2 h charging time during the day and should be switched on in the evening and placed in the room where the child ≤ 5 years of age sleeps. If multiple children ≤ 5 years of age sleep in different locations, one location should be selected. If there are no children ≤ 5 years of age within the household, the Mossie-GO™ device can be placed in an alternative sleeping room.

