Head of household to provide household consent for use of device and participation in the household and acceptability survey (compulsory to take part in the study).Parent/caregiver/guardian of child to provide consent for malaria prevalence sampling at 0, 6 and 12 months via RDT, microscopy and polymerase chain reaction (PCR) (maximum 5600 households, made up of 100 households at baseline and 60 households at subsequent timepoints per cluster with a child ≤ 5 years of age at enrolment in the study, randomly selected at each of the sampling points).Head of household to provide consent for mosquito collection via CDC light trapping (392 households, made up of 7 households in 56 clusters, randomly selected with replacement at each of the sampling points).Head of household to provide consent for mosquito collection via HLCs (30 households, made up of 3 houses in 10 clusters, randomly selected from the subset of households undergoing CDC light trapping with replacement at each of the sampling points).Head of household to provide consent for air sampling (28 households, made up of 2 households in 14 clusters, randomly selected from a subset of the households undergoing HLCs with replacement at each of the sampling points).Head of household, or caregivers or other community members to provide consent for FGDs to assess acceptability of the intervention (8–12 FGDs will take place containing 6–10 participants).

Parent/guardian of a participant may refuse to answer any question or withdraw from the study at any time without any impact to the participant. Study staff can terminate subject participation at any time during the study period if a participant no longer meets the inclusion criteria and/or based on adverse event (AE) or serious adverse event (SAE) assessment.

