### Outcomes {12}

The primary outcome measured in this study will be the average reduction in malaria infection prevalence in children ≤ 5 years of age from baseline to month 12, as measured by RDT and microscopy. Secondary outcome measures include:
CDC light trap indoor density for anophelines and by anopheline species, as measured by light trap collections from 7 pm to 7 am on a 6 monthly basis. Change in mosquito density at baseline and month 12 between arms will be analysed by negative binomial regression with a random effect for study cluster.Anopheline-human contact (indoor and outdoor) using human biting rate (HBR) as an indicator for all anophelines and by anopheline species, as measured by HLC during 6-h intervals on a 6-monthly basis. Change in HBR at baseline and month 12 between arms will be analysed by negative binomial regression with a random effect for study cluster.Anopheline infectivity using sporozoite rate as an indicator for all anopheline and by anopheline species, as measured by laboratory detection of sporozoites in mosquito heads and thoraces from a subsample of anophelines collected during CDC light trap and HLC collections.Insecticide resistance, as measured by WHO tube test bioassay, during the intervention phase. Confirmed resistance, possible resistance and susceptibility will be calculated through evaluating knockdown and mortality rates.Subject behaviour and household features related to exposure to malaria and use of existing control tools, as measured by quantitative and qualitative surveys on a 6-monthly basis. Survey outputs will be summarised using basic statistics.Concentration of transfluthrin in air over the duration of an evening’s use or the Mossie-GO™ and the impact of indoor temperature on the concentration, as measured by air sampling at months 9 and 12. Mean concentration will be compared between arms.Acceptability of Mossie-GO™ in these communities, as measured be quantitative and qualitative surveys at 6 and 12 months and FGDs at 12 months. Outputs will be summarised using basic statistics and thematic analysis.Safety of intervention through monitoring of AEs and SAEs. Measured actively and passively throughout the duration of the study and total number of events and type of events will be compared between study arms.

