## Sample size {14}

Data collected from the study region suggest prevalence of malaria infection by RDT in children ≤ 5 years of age is 20%. A conservative coefficient of variation (CV) of 0.5 for between cluster prevalence was assumed. To detect a 40% reduction in prevalence with 90% power, we need 28 clusters per arm and a sample of 100 children in each cluster. Due to budget restrictions, sample size was reduced after baseline to 60 children in each cluster at 6 and 12 months, resulting in 86% power.

Entomological sample sizes were determined based on logistics, considering budget and personnel restrictions. The sample sizes of similar studies were also considered. For CDC light trapping, sampling will be carried out in all clusters and randomised at the household level. HLCs will be randomised at both the cluster and household level.

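### Human-landing-catch clusters are redrawn every round, so the planned baseline-to-month-12 change in biting rate gains little from baseline and loses precision

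*Protocol article*

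**What the plan says.** Trial design {8}: "A total of 56 clusters will be randomly assigned, in a 1:1 ratio, to one of the two arms", which gives 28 per arm. HLC is done in "3 households within each of 10 clusters (30 households total) at baseline, 6 and 12 months" (Entomological monitoring), and its stated purpose is "to determine the effect of the intervention on the host seeking behaviour of mosquitoes".

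On selection, the same section says "The clusters and households selected for HLCs will be selected at random for each time point". Sample size {14} agrees: "HLCs will be randomised at both the cluster and household level". The consent section {26a} says HLC households are "randomly selected from the subset of households undergoing CDC light trapping with replacement at each of the sampling points".

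On analysis, Outcomes {12} says: "Change in HBR at baseline and month 12 between arms will be analysed by negative binomial regression with a random effect for study cluster".

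The light traps follow a different rule: "For CDC light trapping, sampling will be carried out in all clusters and randomised at the household level" (Sample size {14}). Only their households change between rounds.

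**The concern.** A baseline measurement sharpens a comparison of change when the same units are seen twice, because stable differences between villages then cancel. Here the sampling rule largely prevents that. Most villages caught at month 12 have no baseline catch, and most villages caught at baseline have no month-12 catch. A cluster random effect can link the rounds only through the few villages that happen to be drawn twice. For the rest, between-village variation enters the change once at baseline and again at month 12.

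HLC is the trial's only measure of outdoor biting, since the light traps are indoor. The Introduction and Discussion give outdoor and early-evening biting as a reason for testing spatial repellents. Losing precision on this outcome weakens the entomological support for whatever the primary endpoint shows.

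**Working it through.** **Plan's own figure.** 3 households × 10 clusters = 30 households per round, as stated. No power, effect size or variance is given for HBR, so there is nothing further to reproduce.

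**Overlap between the baseline and month-12 clusters.** Inputs: 56 clusters, with 10 drawn independently in each round. The number shared is hypergeometric (56, 10, 10).
- Expected shared: 10 × 10/56 = 1.79.
- P(0) = 0.114, P(1) = 0.309, P(2) = 0.330, so P(2 or fewer) = 0.754.
- P(6 or more, a majority) = 0.001.
- If each draw were restricted to 5 of the 28 clusters in each arm, expected shared would be 2 × 5 × 5/28 = 1.79. The result does not depend on how the draw treats arm.

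**Precision.** The variances are assumptions, on the log-density scale: cluster variance 1 in each round, correlation ρ between a cluster's two rounds of 0.4 to 0.8, round error variance 0.3, and 5 clusters per arm. The between-arm variance is 2/5 of each value below, so ratios are unaffected.

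| Estimator | Formula | ρ = 0.4 | ρ = 0.8 |
|---|---|---|---|
| Change, same clusters | 2(1 + 0.3) − 2ρ | 1.80 | 1.00 |
| Change, redrawn clusters | 2(1 + 0.3) − 2ρ(5/28) | 2.46 | 2.31 |
| Month 12 only | 1 + 0.3 | 1.30 | 1.30 |
| Month 12, baseline HLC rate as covariate | 1.3 − ρ²/1.3 | 1.18 | 0.81 |

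The factor 5/28 is the expected share of an arm's clusters that recur.

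- Same clusters against redrawn, change score: 1 − 1.80/2.46 = 27%; 1 − 1.00/2.31 = 57%.
- Redrawn change against month 12 only: 2.46/1.30 = 1.89; 2.31/1.30 = 1.78.
- Covariate-adjusted against month 12 only: 1 − 1.18/1.30 = 9%; 1 − 0.81/1.30 = 38%, before the loss of a degree of freedom.

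**Sensitivity to the assumptions.** A second set treats the cluster effect as fully persistent (between-cluster SD 0.25 to 1.0, cluster-by-time SD 0.25 or 0.5) and compares unrestricted redraws with a fixed five-per-arm panel. The standard error of the change is then 1.16 to 4.01 times as large with redrawing. That range also includes chance arm imbalance. The direction is stable, but the size depends heavily on variances that the documents do not give.

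**The case against.** **Not bias.** A reader might infer that comparing mostly different villages biases the result. It does not: random draws from randomised arms are unbiased in expectation.

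**Not shown to be unbalanced by arm.** An unrestricted draw of 10 would split 7:3 or worse with probability 0.295, and 8:2 or worse with probability 0.078. It is tempting to call the selection unbalanced. But the article only says the selection is random; it does not say that arm is ignored. It condenses a fuller protocol that may contain an arm restriction, so this is something to confirm.

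**No z-test is named.** One might add that a normal-theory test on 10 clusters is too liberal (8.6% true error with 8 degrees of freedom). The article specifies only the regression, and the reference distribution belongs in the analysis plan. Two redrawn rounds would also involve about 20 − 1.79 = 18.2 distinct clusters, so 8 degrees of freedom does not describe the planned design.

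**Much of the loss comes from the change score.** This stands. At ρ = 0.4, even a change score on the same clusters (1.80) is worse than month 12 alone (1.30). The advantage of revisiting clusters, properly analysed, is the 9% to 38% in the last comparison. The planned mixed model may also use the few shared clusters somewhat better than a simple difference of means, and the altitude and freshwater-distance covariates in Statistical methods {20a} may absorb some village variation.

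**Redrawing has a purpose.** It spreads the catch over more villages for species and sporozoite description, entomological sample sizes were openly set by logistics, and indoor density is measured in all 56 clusters each round. This limits the importance of the point but does not reconcile the sampling rule with a change outcome.

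**The timeline could suggest a fixed panel.** Participant timeline {13} marks HLC enrolment at month 0 only. The consent section and Entomological monitoring both describe selection at each time point, so the passages need reconciling.

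**Conclusion.** The point holds as a matter of precision. The sampling rule and the outcome definition are both explicit, and they work against each other: about 1.8 of 10 clusters are expected in both rounds, a figure that needs only the stated 10 and 56. Under the assumed variances, the planned change has about 1.8 to 1.9 times the variance of a comparison that ignores baseline. Those ratios rest on the assumed variances and on reading the outcome as a difference in log rates between rounds. A systematic error, a known arm imbalance or an invalid test should not be inferred. Severity is low to moderate: one secondary outcome, sized by logistics, with a nearly free repair.

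**What to change.** Trial status reports baseline and 6-month collection complete and month 12 still to come, so month 12 can be changed.

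1. **Preferred.** At month 12, return to the clusters caught at baseline and redraw households only. Analyse month-12 counts by arm with the cluster's baseline HLC rate as covariate. In a cluster-level analysis this leaves clusters minus 3 degrees of freedom (7 with 10 clusters).
2. **If the clusters cannot be revisited.** Report HBR as a month-12 between-arm comparison, not a change, adjusted for baseline indoor light-trap density, which is planned for all 56 clusters.
3. **Arm split.** Confirm, by coded arm so that blinding is kept, that the HLC clusters are evenly divided. Any cluster added to restore balance has no baseline HLC rate, so its baseline light-trap density must serve instead.
4. **Wording.** Align Outcomes {12}, Participant timeline {13}, the consent section and Entomological monitoring on which clusters are caught in each round.

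**Cost.** No extra catch-nights: still 10 clusters × 3 households × 3 nights. It needs a changed selection list and revised analysis wording. Fewer distinct villages would contribute to species and sporozoite description. Air sampling must also be reconciled: the consent section and Air sampling take 2 households in each of 14 clusters from the HLC households, which cover only 10 clusters in a round, and returning to the same clusters makes that pool no larger.

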##### Air sampling

A geo-spatial temporal profile of transfluthrin concentrations measured in nanograms of diffused transfluthrin will be generated at the 9- and 12-month time points. Air sampling will be conducted in a total of 28 households, made up of 2 households from 14 clusters, selected from the same pool of households undergoing HLCs. Sampling will be conducted at two time intervals, 1 h after device start and then automatically 4 h after that, to determine variation in air availability of transfluthrin. Sampling will take place at a distance between 1 and 4 m from the Mossie-GO™ device and 0.5 m above the ground. After collection, samples will be stored at − 20 °C.

To determine wind direction and strength of air movements, as well as temperature during collections, a long-range wireless wind logger will be set up at 1–4 m height next to the device during the air sampling period. Logging of parameters will be done in 5-min intervals.

### Plans to promote participant retention and complete follow-up {18b}

Participants will receive compensation on completion of each sampling period, i.e. baseline, 6 and 12 months. This will promote participant retention and participation in the next sampling period. They will also be visited monthly by their local VHTs, which will provide an opportunity to raise any concerns or ask questions.

### Data management {19}

#### Data entry

Data will be captured electronically into an ODK Central database via android platforms using ODK software (ODK Collect) and paper-based forms. Electronic data capture is prioritised where sensitive data is being collected as this data will be directly uploaded to the ODK server where it is encrypted and secured. In these cases, paper copies are to be used only as a backup where hard copies are uploaded electronically at a later date or where paper logs are required due to quality assurance compliance.

#### Security and storage

Data entered into ODK will be directly uploaded to the ODK Central server hosted via the London School of Hygiene & Tropical Medicine (LSHTM), where it will be securely stored on encrypted servers with restricted access. Daily backups will be conducted through the LSHTM server and additional weekly backups will be managed and stored offline to prevent data loss. Access to ODK Central will be strictly controlled and limited to delegated members of the study team.

Physical copies of data will be stored in a secure file with restricted access and will be destroyed when no longer in use, after a period of 10 years. Material and data from this study will then be kept for 10 years. This is a legal requirement of the funder. All data will be collected, processed, stored and handled in accordance with the Data Protection Act 2018. Where an ODK form exists that is compatible with the physical copy of data, the data will be uploaded to ODK at the earliest convenience as a primary electronic copy.

#### Processes to promote data quality

Training on electronic data collection through ODK Collect will be provided to all members of the study team and data collectors. Where appropriate, supplementary text is provided within ODK to guide the data collector to use the correct data entry format. For sensitive fields, such as participant ID, there are restrictions on answers to reduce the likelihood of entry errors. Data uploaded to ODK will be downloaded and quality assessed for errors and duplicates.

